**Methods:**

This is a cluster randomized trial with 12 hospital units. The intervention arm receives implementation support for 18 months; control units receive the same support afterwards. The ACP intervention consists of 1. Clinical intervention: ACP; 2. Implementation interventions: Implementation team, ACP coordinator, network meetings, training and supervision for health care personnel, documentation tools and other resources, and fidelity measurements with tailored feedback; 3. Implementation strategies: leadership commitment, whole ward approach and responsive evaluation. Fidelity will be measured three times in the intervention arm and twice in the control arm. Here, the primary outcome is the difference in fidelity changes between the arms. We will also include 420 geriatric patients with one close relative and an attending clinician in a triadic sub-study. Here, the primary outcomes are quality of communication and decision-making when approaching the end of life as perceived by patients and next of kin, and congruence between the patient’s preferences for information and involvement and the clinician’s perceptions of the same. For patients we will also collect clinical data and health register data. Additionally, all clinical staff in both arms will be invited to answer a questionnaire before and during the implementation period. To explore barriers and facilitators and further explore the significance of ACP, qualitative interviews will be performed in the intervention units with patients, next of kin, health care personnel and implementation teams, and with other stakeholders up to national level. Lastly, we will evaluate resource utilization, costs and health outcomes in a cost-effectiveness analysis.

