### The implementation strategies

The hospital units in the intervention arm will receive support through the implementation strategies and implementation interventions for 18 months to be able to use the clinical intervention ACP in routine health care. The control units will provide treatment as usual during this period and receive implementation support after the last fidelity measurement at 18 months.

To secure sustainability, both the evaluation plan and the implementation support emphasise a “whole ward approach” [39]. By this we mean recruiting whole units through the CRCT design (and not only individual patients or next of kin), involvement of all employees, leadership commitment, ACP performed by regular staff, train-the-trainer model, minimal off-site training, freely available ACP-guideline and didactic materials, ACP-invitations to all patients in the units who are able to participate, encouraging next of kins’ participation, and supported decision-making if the patient is cognitively impaired [50]. We have recently used parts of this approach in an ACP-study in nursing homes [39, 51]. Our results demonstrate significant improvement of user and family involvement on entire units, not only for patients offered ACP [52].

The implementation support starts with a kick-off for all units. An initial meeting with all involved parties at each unit is recommended. All participating units will recruit a local coordinator for the project. Furthermore, the intervention units assign an implementation team, consisting of one or more health care professionals and the unit leader, which will ensure the local implementation. The project group will provide, in a train-the-trainer model, training and supervision for these local resource persons. We will encourage the implementation teams to meet 1–2 times monthly in the intervention period, and the project group will have monthly joint meetings with the teams digitally. The results from the detailed fidelity assessments (described below) will be used to provide tailored feedback to each intervention unit three times during the implementation period (formative evaluation). Additionally, during the 18 months of intervention, we will gather the implementation teams across all the intervention units in network meetings every sixth month for networking and discussion. Written notes from these meetings will be included in the qualitative evaluation study (see below).

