#### Data collection

We defined baseline as the situation before the start of the intervention, and the baseline fidelity measurements were conducted from May to August 2022. The participating hospital units were randomized to the intervention- or control arm after the baseline fidelity measurement in August 2022. The implementation period started with kick-off on Oct 25th, 2022, and will continue for approximately 18 months (when the inclusion for the triadic sub-study is completed, and before the last measurement of fidelity). Fidelity measurements in the intervention arm will be at baseline, at 7–10 months after the start of the intervention (May to August 2023) and at 18 months (April 2024). Fidelity measurements in the control arm will be at baseline and at 18 months. The second fidelity measurement is not done in the control group due to resource considerations, and to avoid influencing clinical activity in the control arm.

The fidelity scores at each unit will be based on a) interviews with leaders, b) interviews with resource persons, c) interviews with physicians, d) interviews with nurses, e) written material (e.g., information brochures or clinical procedures) and f) existing routine data (number of patients eligible for/offered/received ACP). Seven of the project members participate in the data collection, forming teams of two people visiting each site. Based on the interviews and available information, the two researchers will, at the end of the visit, score fidelity individually, and subsequently discuss possible discrepancies and decide on a consensus score.

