### Clinical effectiveness – The triadic sub-study with patients, next of kin and clinicians

In this sub-study, we will assess and compare ACP relevant outcomes between the intervention arm and control arm. As described, we use a triadic approach, by recruiting each patient together with a close relative, and an attending clinician. This allows us to assess and compare the perspectives of all three stakeholders across the two study-arms. We aim to include at least 420 triads in total from the two arms. Each person in each “triad” will complete a questionnaire inspired by past ACP-, end-of-life- and shared decision-making studies and adapted to the Norwegian context and the current study. Paper questionnaires will be used for patients, the next of kin can choose between paper and digital questionnaires and digital questionnaires will be used for the clinicians. The patients will be offered assistance in filling out the questionnaire by a staff not involved in the treatment of the patient. The inclusion of participants will start approximately 13 months after the start of the intervention in the implementation arm.

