##### Data from national registries

The patient dataset will be coupled to individual data from national registries (from 18 months before to 18 months after inclusion (or until death). This allows description of the patient population and their use of health services, and to assess possible long-term effects of ACP. The registers include the Norwegian Registry for Primary Health Care, Norwegian Patient Registry, Norwegian Prescription Database and Norwegian Cause of Death Registry.

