### Health economics

The economics analysis includes estimation of healthcare utilization, costs and cost-effectiveness of ACP and the implementation support in geriatric hospital units compared to standard of care. We will identify the resource use and costs related to implementing and conducting ACP in clinical practice, and we will estimate patient’s healthcare utilization and costs in order to identify differences in pathways as a result of implementation of ACP. Higher costs after implementation may indicate underutilization and lower costs may indicate overutilization of healthcare without ACP. The information on healthcare utilization will be collected from national registries covering both pharmaceuticals and primary, secondary, home based and institutional based care.

Resource use and healthcare utilization will be summarized over 18 months prior to inclusion in the trial and 18 months after. Total costs will be calculated, and we will use regression analysis to estimate the effect of ACP on total costs, also adjusting for individual characteristics, such as age, gender, comorbidity, living situation, social network, marital status and education measured at inclusion. We will also estimate the cost-effectiveness of implementation of ACP compared to standard of care. The costs will include intervention costs of ACP and the cost of the hospital stay. Differences in costs will be compared to the primary outcomes (measured as percentage point difference in quality of communication and decision-making for patients and for next of kin, congruence (attending clinicians) and fidelity (implementation outcome) and selected secondary outcomes. We will use the incremental cost-effectiveness ratio, defined as differences in costs between implementation of ACP compared to standard of care divided by percentage difference in primary (selected secondary) outcomes (ACP and standard of care). Uncertainty will be estimated by bootstrap methods and displayed in a cost-effectiveness plane.

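### The 18-month utilisation and total-cost contrast is labelled ACP versus standard of care, although control units start the same support while their patients are still being followed

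*Protocol article*

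**What the plan says.** Four statements in the protocol article meet on this point.

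- **Control arm.** The section on implementation strategies states: "The control units will provide treatment as usual during this period and receive implementation support after the last fidelity measurement at 18 months". The abstract adds that "control units receive the same support afterwards". The Data collection section under the fidelity outcome dates the last measurement to April 2024.
- **Enrolment.** For the triadic sub-study, "The inclusion of participants will start approximately 13 months after the start of the intervention". Table 1 gives months 13 to 18 for the questionnaires. The implementation period is to end "when the inclusion for the triadic sub-study is completed, and before the last measurement of fidelity".
- **Follow-up.** In Health economics: "Resource use and healthcare utilization will be summarized over 18 months prior to inclusion in the trial and 18 months after". The section on national registries uses the same window, truncated at death, and gives as one purpose "to assess possible long-term effects of ACP".
- **Comparator.** Health economics names standard of care as the comparator, plans a regression for the effect of ACP on total costs, and reads higher or lower costs after implementation as possible signs of under- or overuse of care in the absence of ACP.

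No section shortens the window, censors at the start of control support or redefines the comparator. The Discussion treats contamination only as control units taking up ACP of their own accord during the project period, which it considers unlikely. It does not mention the planned handover in this connection.

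**The concern.** The cost interpretation needs a control arm that stays without systematic ACP for the 18 months being costed. The schedule provides for such an arm only up to the month-18 measurement, and patients join it in the five months before that date. For most of the window, the control patients' home unit may be receiving the programme under test.

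There is a plausible route to exposure. The patients are frail and acutely ill, and the units serve separate catchment areas, so a readmission can return to the same hospital. The article also reports, from earlier nursing-home work with parts of this approach, that involvement improved across whole units and not only among patients offered ACP.

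If later ACP in control patients acts in the same direction as ACP at the index stay, it pulls the long-term contrast towards zero. At stake is the reading of a null result: little difference in 18-month cost could be reported as ACP not changing utilisation, when the comparison made was early against possibly later access.

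**Working it through.** The plan gives no figure for this overlap, so there is none to reproduce. The check is calendar arithmetic.

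**Inputs from the article**
- Kick-off: 25 October 2022, taken as month 0.
- Enrolment month *e*: about 13 to 18.
- Follow-up: 18 months from inclusion, or until death.
- Control support: after the month-18 measurement. No exact start date is given, so month 18 is an assumption and the earliest case.
- Patients: 12 units × 35 = 420. An equal split gives 210 per arm.

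**Overlap**

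Follow-up ends at month *e* + 18. The months after month 18 are (*e* + 18) − 18 = *e*. The months before it are 18 − *e*.

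| Enrolled at month | Follow-up ends at month | Months before control support | Months after | Share after |
|---|---|---|---|---|
| 13 | 31 | 5 | 13 | 13/18 = 72% |
| 15.5 | 33.5 | 2.5 | 15.5 | 15.5/18 = 86% |
| 18 | 36 | 0 | 18 | 18/18 = 100% |

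With uniform enrolment (assumption) the mean is 86%. Before deaths, that is 210 × 15.5 = 3,255 of 210 × 18 = 3,780 control person-months.

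**Allowing for a lag**

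Let ACP reach routine practice in control units *L* months after month 18, through a later start, slow uptake or both. The overlap is then *e* − *L*. The values of *L* are assumptions. Four months mirrors the first planned patient interviews in the intervention units, and 13 months mirrors the wait before triadic enrolment there.

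| *L* (months) | Overlap, *e* = 13 to 18 | Mean share |
|---|---|---|
| 0 | 13 to 18 | 15.5/18 = 86% |
| 3 | 10 to 15 | 12.5/18 = 69% |
| 4 | 9 to 14 | 11.5/18 = 64% |
| 6 | 7 to 12 | 9.5/18 = 53% |
| 13 | 0 to 5 | 2.5/18 = 14% |

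Deaths also reduce it. With a constant hazard and assumed 18-month mortality of 30% to 70%, the mean share of control person-time is 84% to 79% with no lag and 48% to 38% with a 6-month lag.

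**From overlap to dilution**

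This step cannot be computed, because the article gives neither a readmission rate nor an expected uptake of ACP in control units after handover. As an illustration only, suppose a share *q* of control patients later receive ACP and it has its full effect on them. The retained contrast is 1 − *q*, and the sample needed for the same power grows by 1/(1 − *q*)²:

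- *q* = 10%: 90% retained, 1.23 times the sample.
- *q* = 25%: 75% retained, 1.78 times.
- *q* = 50%: 50% retained, 4.0 times.

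The full-effect assumption is severe, since ACP received part-way through the window can affect only what follows it.

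**The case against.** The strongest reply is that calendar overlap is not exposure. A control patient is exposed only if alive, readmitted to that unit and reached by ACP there. The article says that many geriatric patients go to other medical wards, and the programme is designed to take time to become routine. This stands: 72% to 100% is the no-lag upper bound for units. A reader might infer from it that most control patients are contaminated; the documents do not support that.

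Secondly, ACP in the triadic study belongs to the index stay. Intervention patients are excluded if it is not held before discharge, and control index stays fall under usual care. This also stands. A reader might infer that the whole economic evaluation lacks a valid comparator. That goes too far: questionnaire data are collected at months 13 to 18 and fidelity is measured before control support begins. The ICER costs are named as the ACP intervention and the hospital stay; if the latter is the index stay, the ratio is largely untouched.

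Thirdly, a reader might extend the point to the 18 months before inclusion, most of which follow kick-off. The article does not call that window a pre-intervention baseline or plan to adjust for it. The listed covariates are individual characteristics at inclusion, and patients with ACP before the current admission are excluded in both arms. No criticism follows, and a pre-kick-off covariate would not be workable, since the window holds only 18 − *e* = 0 to 5 such months.

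Finally, delayed support is openly stated, and a censored analysis could sit in a plan that is not shown. That explains the absence of the analysis but not the stated comparator, which conflicts with the article's own schedule. The sample size increase from 22 to 35 per cluster does mention control patients receiving ACP, but it also covers missing data, its parts are not separated, and it was set for the questionnaire outcomes.

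**Conclusion.** The point holds for the 18-month registry utilisation, the total-cost regression and the long-term-effects aim. On the stated dates, control units are certain to be under usual care for only the first 0 to 5 of each patient's 18 follow-up months. The remaining 13 to 18 months fall after support begins if it starts at month 18, and fewer if it starts later.

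The consequence is a dilution of unknown size, most likely towards no difference, provided later ACP acts in the same direction as index-stay ACP. The randomised comparison remains valid as early against delayed access; the label and the reading of a null result are what fail. The primary questionnaire and fidelity outcomes are not in question.

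**What to change.** 1. In the Health economics and national registries sections, describe the 18-month contrast as ACP at the index admission under immediate support versus usual care with delayed support, analysed by intention to treat. State that a null result does not show that ACP leaves utilisation unchanged.
2. Pre-specify a supporting analysis of utilisation and cost that censors both arms at the same calendar date, when control-unit support starts. Record that date, and account for the differing length of follow-up between patients.
3. Where the record review is carried out (the article makes it conditional on resources), report ACP received after inclusion by arm, so that readers can judge the dilution.
4. State whether the hospital stay in the ICER is the index stay.

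The cost is wording and analysis work; design and recruitment do not change. The drawback is precision. The pre-crossover window is 0 to 5 months per patient, with none for the latest enrolled. Under uniform enrolment it averages 2.5 months, or 210 × 2.5 = 525 person-months per arm before deaths. The censored analysis can therefore support the 18-month result but not replace it.

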## Methods

### Trial design

The project is a multicentre cluster randomized controlled trial (CRCT). Each participating geriatric unit, with responsibility to provide medical care to acutely admitted older medical patients, constitutes one cluster and is the unit of randomization. Figure 1 gives an overview of the study design. The article conforms to the Standard Protocol Items: Recommendations for Interventional Trials (SPIRIT) [36] (Additional file 1), and the study results will reported in accordance with the Consort 2010 extension to cluster randomized trials. All methods carried out in the study will be performed in accordance with relevant guidelines and regulations.

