The units were sorted from one to 12 according to the number of geriatric beds and then stratified into three strata: four clusters with 16 to 23 beds, six clusters with 6 to 10 beds and two clusters with 4 and 5 beds respectively. In each block, the clusters were randomized to either the intervention or the control arm with an allocation ratio of 1:1. An independent professor in epidemiology performed the allocation using the Microsoft Excel RAND-function, only knowing the numbers of the clusters. The randomization was performed to achieve a balance in unit types in the intervention and control arm and a similar size of the two arms including a similar number of admitted patients filling the inclusion criteria. All hospitals are located in cities or towns. The purpose of the stratification was primarily to achieve a balance in the number of patients and next of kin between the two arms, and secondly to include units of various sizes in both.

The study has primary outcomes for the implementation and for the clinical effectiveness. The primary outcome for the implementation outcome sub-study is the differences in fidelity changes between the arms. The unit of analysis for the fidelity scores is the health care units or clusters. Fidelity is rated on 5-point scales (1 = poor fidelity, 5 = high fidelity). Based on previous research (mean difference 1.82 and average SD 0.80 after 18 months with implementation support), we have calculated that we need at least four clusters in each arm to show that implementation support gives a significant increase in fidelity, based on 5% two-tailed significance and 80% power. If the differences are smaller in our study, we will need a larger sample. Due to the possibility of unit drop-out during the project period and to secure sufficient power, we have included six units in the intervention arm and six in the control arm.

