The primary outcomes for the clinical effectiveness study “The triadic sub-study with patients, next of kin and clinicians” are described under “outcomes”. The unit of analysis is the individuals recruited in each cluster. Since we have not found comparable studies that have published data on these instruments, we decided to use a 0.5 SD improvement (medium effect) when calculating the sample size. Based on a 0.5 SD increase in the primary outcome and an Intra-class Correlation Coefficient (ICC) of 0.05, we need 132 patients in each arm or 22 per cluster with six clusters in each arm to achieve 80% power to detect a difference in the primary outcome among patients, between groups with a certainty of 95%. Taking into account the possibility of patients in the control arm receiving ACP, and incomplete or missing data, we aim to recruit at least 35 patients per cluster. A similar power calculation with the same conservative assumptions has been done for the primary outcomes for next of kin and clinicians with the same results (35 next of kin and 35 clinicians per cluster).

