#### Data analysis

Demographic and clinical data about the patients will be used to assess whether the patients in the control and intervention units are comparable. In addition, the participating units will collect basic and anonymous clinical information about all patients admitted to the units at shorter random time periods, to get more information about the participant units and to compare the included patients with all admitted patients.

Number and percentages of invitation to and participation in ACP for patients and next of kin will be calculated and compared between intervention and control group. The primary statistical analyses will be the difference in mean outcomes between participants in the intervention and the control group using linear mixed effects models. The random part of the model will consist of random intercept for patient or relative identification nested within centre. Missing data will be handled by multiple imputation using predictive means matching with 100 imputed data sets.

If the analyses show differences in the intervention and control arm, we will perform analyses to assess if higher fidelity score (higher levels of implementation) is associated with improved outcomes for patients, next of kin, and clinicians. For the secondary outcomes, we will compute average outcomes and SD for the intervention and the control group and use the t-test to determine if there is a significant difference between groups.

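### The cost regression is specified with individual covariates only and no hospital-unit term, and the bootstrap's resampling unit is not stated, although 12 units were randomised

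*Protocol article*

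**What the plan says.** The Trial design section states that each geriatric unit "constitutes one cluster and is the unit of randomization". The section on selection, allocation and sample size adds that "we have included six units in the intervention arm and six in the control arm".

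For costs, the Health economics section says "we will use regression analysis to estimate the effect of ACP on total costs, also adjusting for individual characteristics". The examples that follow are age, gender, comorbidity, living situation, social network, marital status and education. All describe the patient, and no unit or centre term appears. For the cost-effectiveness ratio the section says "Uncertainty will be estimated by bootstrap methods and displayed in a cost-effectiveness plane" and does not name what is resampled. It sets cost differences against the patient, next-of-kin and clinician outcomes and also against fidelity, which the article analyses at unit level.

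Elsewhere the article is explicit about clustering. The fidelity section names random intercepts for clusters in its mixed models, and the triadic primary analysis names a random intercept nested within centre. For the triadic secondary outcomes it will "use the t-test to determine if there is a significant difference between groups", with no cluster term, and the staff questionnaire is treated the same way.

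**The concern.** When units are randomised, the arm comparison carries the variation between units as well as that between patients. A regression with only patient covariates treats about 420 patients as independent observations. Costs could well differ by unit here. Each unit serves its own catchment area, the units differ in size and organisation, some include stroke beds, and the costs cover primary, home-based and institutional care as well as hospital care.

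What is at stake is the stated precision of the cost difference and of the cost-effectiveness plane. Health economics is a secondary objective, but the Discussion presents it as evidence for service planning.

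The bootstrap raises a further issue. Fidelity has one value per unit, so 12 values in all. Resampling patients cannot express uncertainty in a unit-level outcome, so for the fidelity ratio at least, units must be resampled.

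**Working it through.** **The plan's own figure.** The article states no precision or power figure for costs, so the check starts from its sample size for the patient questionnaire outcome. It assumes "Based on a 0.5 SD increase in the primary outcome and an Intra-class Correlation Coefficient (ICC) of 0.05" and concludes that "we need 132 patients in each arm or 22 per cluster with six clusters in each arm to achieve 80% power".

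- Individually randomised n per arm for 0.5 SD, two-sided 5%, 80% power, from the t-test: 63.77.
- Cluster size for k = 6 clusters per arm: m = n(1 − ICC)/(k − n × ICC) = 63.77 × 0.95/(6 − 63.77 × 0.05) = 21.5, rounded up to 22.
- 6 × 22 = 132 per arm, which matches.

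The sponsor therefore accounted for clustering when sizing the triadic study, using ICC 0.05.

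**Inputs for the cost analysis.**

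- 12 units, six per arm, with a target of 35 patients per unit (420 in total), all from the article.
- ICC for costs: not given. I assume 0.01 to 0.05. The upper end is the article's value for questionnaire outcomes. The ICC that matters is the one remaining after covariate adjustment.

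**Formulas.** Design effect DE = 1 + (35 − 1) × ICC. The standard error is too small by √DE. The true error of a nominal 5% test is 2 × (1 − Φ(1.96/√DE)).

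| Assumed cost ICC | DE | √DE | Effective n (420/DE) | True error | Coverage of nominal 95% interval |
|---|---|---|---|---|---|
| 0 | 1.00 | 1.00 | 420 | 5% | 95% |
| 0.01 | 1.34 | 1.16 | 313 | 9% | 91% |
| 0.02 | 1.68 | 1.30 | 250 | 13% | 87% |
| 0.05 | 2.70 | 1.64 | 156 | 23% | 77% |

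Beyond the assumed range, ICC 0.10 gives DE 4.40, a factor of 2.10 and a true error of 35%. Equal unit sizes are assumed.

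**What the choice of bootstrap does.** I simulated data with no true difference: six units per arm, 35 patients per unit, 1,500 runs, percentile intervals. The data were normal; costs are usually skewed, so the rates are illustrative. The nominal rate is 5%.

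| Method | ICC 0.01 | ICC 0.05 | ICC 0.10 |
|---|---|---|---|
| Resample patients | 9% | 26% | 38% |
| Resample whole units | 10% | 12% | 12% |
| Resample units, then patients | 2% | about 4–5% | 7% |
| t-test on unit means (10 degrees of freedom) | 5% | 5% | 5% |

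Resampling units avoids the large error at the higher ICCs, but no simple bootstrap is exact with six units per arm.

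**The case against.** The strongest reply is that this is silence in a condensed article. The section names a regression and a bootstrap but gives no error structure, variance estimator or resampling scheme. A list of fixed covariates does not describe the random part of a model, and such detail for a secondary economic analysis often sits in a separate plan. The article respects clustering in its sample size and primary models, and commits to the CONSORT extension for cluster trials.

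Part of this stands. A reader might infer that the bootstrap is planned at patient level, or that cost uncertainty is certain to be understated. The article supports neither: the resampling unit is unstated, and understatement requires that units are in fact ignored and that the cost ICC is above zero. The t-tests elsewhere are a separate matter and do not show how costs will be analysed.

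The reply does not remove the point. The article gives the outcome, the exposure and the kind of adjustment for the cost model. The list is open-ended, but only towards further individual characteristics. Where the authors intend a cluster term they say so, and some analyses in the same article have none, so a unit term cannot be taken as implied.

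The exposure wording (effect of ACP rather than of allocated arm) is a minor matter. The section frames cost-effectiveness as implementation against standard care, and intervention patients without an ACP conversation are excluded. The two can therefore differ only through ACP in control patients. The sample-size section allows for this and the Discussion thinks ACP implementation in control clusters unlikely. Naming the arm would settle it.

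**Conclusion.** The point holds conditionally. As written, the cost regression has only individual covariates and no unit term, and the bootstrap's unit is left open. Run that way with a cost ICC above zero, it understates the standard error by a factor of about 1.16 to 1.64 and gives a true error of about 9% to 23% at a nominal 5%. This rests on an assumed ICC of 0.01 to 0.05, 35 patients in every unit and no other allowance for clustering. At an ICC of zero the design effect causes no understatement. The affected objective is secondary, but correcting the wording is cheap and should be done before the cost data are analysed.

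**What to change.** - **Regression.** Regress post-inclusion total cost on allocated arm, with a random intercept for hospital unit, small-sample degrees of freedom and the randomisation stratum. Keep the individual covariates and add the 18-month pre-inclusion cost, which the section already plans to summarise but does not list for adjustment.
- **Bootstrap.** State that units are resampled within arm, with or without a second stage for patients. The ratio that uses fidelity needs this in any case.
- **Small number of units.** Report that bootstrap intervals from six units per arm are approximate, and give a small-sample or unit-level analysis of the cost difference as a check.

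**Cost.** No new data and slightly more analysis work. Intervals will usually be wider. With a t reference on 10 degrees of freedom (critical value 2.23), the ratio to the naive width is √DE × 2.23/1.96: about 1.3 at ICC 0.01 and 1.9 at ICC 0.05, before any gain from adjusting for prior cost. Including the three strata leaves 12 − 4 = 8 unit-level degrees of freedom, which widens them a little further.
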